### Study flow

Study flow and schedule is presented in figure 1 and table 2. Patients are recruited at urology outpatient clinic at urologists’ visits. If the inclusion criteria are met and the exclusion criteria are not and the participant signs informed consent form, he is given a study number (ranging between E-001 to E-400) and he receives either 80 mg atorvastatin or placebo according to the study arm randomly allocated for the study number. No blocking or other restrictions will be implemented for randomisation. Only the national study coordinator in each country will be able to see which study arm the participant has been randomised to. The participant will then receive first dose of the respective study drug randomised to his study number. The drug boxes and capsules containing atorvastatin and placebo will be identical in appearance. All researchers, nurses and study participants will remain blinded to the allocation sequence until termination of the study and closure of the study data.

**Table 2 T2:** Study flow and timing of the laboratory and blood sample collection

	Enrolment	Allocation	Follow-up‡			
Timepoint		0	6 months	12 months	18 months	24 months
Enrolment:						
Eligibility screen	x					
Informed consent	x					
Allocation		x				
Interventions:*						
Atorvastatin			x	x	x	x
Placebo			x	x	x	x
Assesments:						
Serum PSA (ng/mL)	x		x	x	x	x
Alkaline phosphatase (U/L)	x		x	x	x	x
Creatinine (µmol/L)	x		x	x	x	x
Serum creatine kinase (U/L)	x		x	x	x	x
Alanine aminotranspherase (U/L)	x		x	x	x	x
Fasting blood glucose (mmol/L)	x		x	x	x	x
Lipid levels (total cholesterol, LDL, HDL and triglycerides) (mmol/L)	x		x	x	x	x
Cell free DNA (subgroup)†	x					
QoL	x			x		x

*Allocation 1:1 to have eighter 80 mg atorvastatin or placebo daily

†Cell free DNA is measured before allocation and after occurrence of castration resistance.

‡Follow-up until disease recurrance, death or max. 10 years

HDL, high-density lipoprotein; LDL, low-density lipoprotein; PSA, prostate-specific antigen; QoL, quality of life.

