### Sample size calculation

In a cohort study by Harshman *et al*,^23^ among men starting ADT, 58% of the statin users and 75% of non-users of statins progress to castration resistance during median 5.8 years. We used these crude percentages for sample size calculations.

With alpha and beta values of 0.05 and 0.20 (power=0.80), sample size of 400 men will be enough to detect a risk difference with HR 0.65 (figure 2). We assume 10% drop-out rate in each study arm. The programme ‘PS—Power and sample size, V.3.1.2’ was used for the calculation.

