**Figure 2 F2:**
[figure not shown]
Sample size estimation with power 0.8 as a function of HR. Calculation was made based on study by Harshman *et al.*^23^

The median time to disease progression is assumed to be 12–15 months for patients with de novo metastatic disease and 33 months for patients recurring after primary therapy.^3–7^ Therefore, the intervention will continue until castration resistance, death, or for maximum of 10 years. Post hoc follow-up will continue after the intervention. A 3 months’ difference in time to castration resistance between the study arms will be considered clinically significant.

It has to be noted that the number of studies published on this topic is low and, in the absence of randomised evidence on this topic, the power calculation is based on results of epidemiological study prone to residual bias. Therefore, an interim analysis will be performed after the first 100 participants have met the primary endpoint, that is, progressed into castration resistance. Without lifting the blinding, the power calculations are repeated to verify whether the chosen sample size has adequate statistical power to detect statistically significant difference of the effect size observed between the randomisation groups at that time. If the calculations suggest that a larger sample size is needed for the trial, the study protocol will be amended with updated recruitment target.

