### Statistical methods

Distribution balance of PCa clinical characteristics such as TNM stage at diagnosis, Gleason score and PSA at time of diagnosis will be presented in a patient characteristics table, stratified by study arms. Categorical variables are displayed as absolute count frequencies and relative frequencies, that is, proportion within study arm. Continuous variables are presented as median and IQR. Minimum and maximum values are not shown to ensure anonymity of the participants.

Recurrence-free survival, that is, time from ADT initiation to castration resistance, will be analysed by using Kaplan-Meier (KM) estimator, stratified by study arm. The statistical significance of the difference between the survival estimates is tested with log-rank test. No adjustments will be used for KM estimator as the study intervention is randomised. Risk of death, as well as risk for occurrence of adverse tumour traits among men receiving atorvastatin compared with men receiving placebo will be estimated using Cox proportional hazards regression.

Univariate analysis of changes in serum lipid levels is performed by calculating the difference after—before for each participant. The statistical significance of the difference between the study arms is analysed by Mann-Whitney U test (or by t-test if under normality). These results are complemented with boxplots. Multivariable analysis for difference in serum lipid levels between the study arms are performed by fitting a logistic regression model such that the study arm is used as the response variable whereas lipid level differences are used as predictors (ie, each lipid level difference as an independent predictor). Lipid levels are expected to display heavy multicollinearity; therefore, variance inflation factors (VIF) are calculated for each coefficient afterwards, and possible adjustments made by dropping predictors with extreme VIFs (>10).

The occurrence of adverse tumour genomic traits will be analysed by calculating the proportion of participants developing adverse tumour genomic traits. The statistical significance between the proportions is tested by proportions test.

The WHOQOL-BREF patient-reported outcome (PRO) of the quality-of-life is analysed by tabulating absolute and relative frequencies. χ^2^ test for homogeneity is used to test the statistical significance of the difference between the study arms of each PRO item.

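### The primary log-rank test ignores disease setting, although the plan assumes a more than two-fold difference in median time to progression between the two settings; stratifying would gain about 3 to 7 points of power at little cost

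*Protocol article*

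**What the plan says.** All references are to the protocol article.

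- **Statistical methods.** Time from start of ADT to castration resistance is described by Kaplan-Meier curves for each arm, and "The statistical significance of the difference between the survival estimates is tested with log-rank test". No strata are named. The curves are said to be stratified by study arm, but that is the treatment comparison, not a prognostic stratum. The section then states: "No adjustments will be used for KM estimator as the study intervention is randomised".
- **Study flow.** "No blocking or other restrictions will be implemented for randomisation".
- **Sample size calculation** (text after Figure 2). Median time to progression is "assumed to be 12–15 months for patients with de novo metastatic disease and 33 months for patients recurring after primary therapy".
- **Study setting** and **Inclusion and exclusion criteria.** Both groups are enrolled. Their expected shares are not given.
- **Statistical methods, subgroup analyses.** These are by type of ADT, local therapy and additional systemic therapy. Local therapy overlaps with disease setting, but none of these factors enters the primary test.

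**The concern.** The plan itself names a strong prognostic factor: the ratio of the assumed medians is 33/15 = 2.2 to 33/12 = 2.75. It then uses that factor neither in the randomisation nor in the primary test, and the only reason given is that treatment is randomised. That reason answers a question about systematic bias. It does not answer the question of efficiency. When men with very different hazards share one risk set, part of the outcome variation that disease setting explains is left in the comparison, and the test loses power.

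The article shows why this matters here. It says that the assumed effect comes from epidemiological data open to residual bias, it plans to repeat the power calculation after 100 events and possibly to raise the recruitment target, and it expects enrolment to take several years. Power recovered in the analysis is cheaper than power recovered by recruiting more men.

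**Working it through.** **1. The plan's own figure.** The article states that a "sample size of 400 men will be enough to detect a risk difference with HR 0.65", at alpha 0.05 and power 0.80, with 10% drop-out. Two-sided alpha is assumed here, since the article does not say.

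- Events for HR 0.65 (Schoenfeld): 4 × (1.960 + 0.842)² / (ln 0.65)² = 169.2, so 170. Freedman's formula gives 175.
- Mean event proportion: (58% + 75%)/2 = 66.5%.
- Men needed: 170/0.665 = 256 to 175/0.665 = 264, or 285 to 294 after dividing by 0.9.

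The figure of 400 is not reproduced from the stated inputs, but it is not contradicted as sufficient: 400 × 0.665 = 266 events give 94% power, and 360 evaluable men give 91.5%. The point below does not depend on this.

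**2. Simulation of both tests.**

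- From the article: 400 men, 1:1 simple randomisation, medians 12 to 15 and 33 months, HR 0.65, 10% drop-out, at least 12 months of follow-up after recruitment.
- Assumed, because the article gives no figure: 50% de novo (range 30 to 70%), 48 months of uniform accrual (range 36 to 60), exponential times, and the same HR in both settings.
- 4,000 trials per scenario. The Monte Carlo standard error of a power near 84% is √(0.84 × 0.16/4000) = 0.6 points.

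| De novo median / share / accrual + minimum follow-up (months) | HR | Events | Unstratified | Stratified |
|---|---|---|---|---|
| 13.5 / 50% / 48+12 (base) | 0.65 | 225 | 83.8% | 88.7% |
| 12 / 30% / 48+12 | 0.65 | 207 | 80.6% | 86.7% |
| 12 / 50% / 48+12 | 0.65 | 232 | 83.6% | 90.2% |
| 15 / 70% / 48+12 | 0.65 | 239 | 87.8% | 90.9% |
| 13.5 / 50% / 36+12 | 0.65 | 205 | 80.9% | 85.7% |
| 13.5 / 50% / 60+12 | 0.65 | 242 | 86.7% | 91.9% |
| 13.5 / 50% / 48+36 | 0.65 | 294 | 90.5% | 95.7% |
| 13.5 / 50% / 48+12 | 0.70 | 230 | 70.6% | 77.1% |
| 13.5 / 50% / 48+12 | 0.75 | 234 | 52.5% | 59.2% |
| 13.5 / 50% / 48+12 | 0.80 | 238 | 34.2% | 39.3% |

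Over all scenarios at HR 0.65 the gain is 3.1 to 6.6 points. A simpler set-up with 360 evaluable men and no partial follow-up from drop-outs gives 82.7% against 87.9 to 88.8% in the base case, and about 50% against 57% at HR 0.75.

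**3. Size in terms of information.** Base case: power 83.8% corresponds to 1.96 + 0.986 = 2.946, and 88.7% to 1.96 + 1.211 = 3.171. (2.946/3.171)² = 0.863, so the unstratified test gives up about 14% of the information. The range over scenarios is about 10 to 21%.

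**4. Type I error.** Under no effect, rejection in the direction of benefit was 3.0% unstratified and 2.9% stratified, against a nominal 2.5% with standard error 0.25 points. A two-sided check gave about 5% for both tests.

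**5. Estimated HR.** With 0.65 within each setting, the pooled Cox HR averaged 0.673 in the base case (0.663 to 0.680 over scenarios). The stratified HR averaged 0.651.

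**6. A smaller prognostic difference.** With medians of 21.2 and 33 months (ratio 1.56), power is 82.2% unstratified and 83.3% stratified.

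**The case against.** **The test is valid and matches the design.** An unstratified log-rank test after unrestricted randomisation is sound. This stands. A reader might infer that the test is biased or that type I error is inflated; step 4 shows no difference between the two tests.

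**The power target is met.** Unstratified power was about 81 to 91% in every scenario with 400 men and HR 0.65. This also stands, so it would be wrong to infer that the trial is underpowered for this reason. One could obtain lower figures by analysing at exactly 169 events (72.9% unstratified, 78.5% stratified), but the protocol has no such rule: unblinding follows full recruitment plus at least 12 months for every participant.

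**The HR is not biased.** A reader might take 0.67 against 0.65 as an error of estimation. It is the difference between a marginal and a within-setting HR, because the HR is not collapsible. The planning figures were themselves crude: 58% and 75% give ln(0.42)/ln(0.25) = 0.63 under exponential times. If 0.65 is meant as the pooled HR (about 0.63 within setting), power is 87 to 88% unstratified and 91 to 93% stratified. A gain remains, but nothing is lost against the plan.

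**The ratio of medians is soft.** The Introduction gives time to castration resistance for metastatic men but failure-free survival for recurrent men. On the one endpoint given for both, death at 45 and 70 months, the ratio is 70/45 = 1.56 and the gain is about 1 point. This limits the weight of the finding.

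**Chance imbalance is a weak argument.** With 50% de novo and 200 men per arm, the between-arm difference in share has SD √(0.25 × 2/200) = 5 points. A 5-point imbalance shifts log HR by about 0.05 × ln(33/13.5) = 0.045, a third of the standard error 2/√225 = 0.13. The test's error rate already allows for this.

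**The sentence concerns the Kaplan-Meier estimator, and a detailed analysis plan is announced.** Both are true. But the log-rank test is also described without strata, and the article states a choice with a reason rather than leaving the matter open.

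**Conclusion.** The point holds as one of efficiency. The primary test is valid but weaker than it could be, and randomisation, the only reason given, does not bear on that.

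Under the plan's medians and a within-setting HR of 0.65, stratifying adds about 3 to 7 power points, from about 83% to 88% in the base case. At HR 0.75 the gain is from about 50% to 57%, which matters more because the plan doubts its own effect size. With a ratio of medians near 1.6 only 1 to 2 points remain. These sizes rest on assumed case mix, accrual, exponential times, a common HR in both settings and two-sided alpha. The gain was positive in every scenario tried.

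A reader might add that no effect estimator is named for the primary endpoint, since Cox regression is listed only for death and adverse tumour traits. That detail is commonly left to an analysis plan, and one is announced, so it is not a fault of this document.

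**What to change.** Before any unblinding, in the protocol or the announced analysis plan:

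1. Make the primary test a log-rank test stratified by disease setting at entry, de novo metastatic versus recurrent after primary treatment.
2. Define that variable from the eligibility data, with a written rule for every participant, including men whose recurrence is already metastatic.
3. Take any HR reported for the primary endpoint, with its 95% CI, from a Cox model with the same strata, and describe it as a within-setting estimate.
4. Keep the unstratified Kaplan-Meier curves and log-rank test as supportive analyses.

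The cost is small. The randomisation list can stay as it is, and no new procedure is needed for participants. The article does not define a disease-setting variable, but the eligibility criteria imply that it is known, so it must be derived and checked. The HR also changes meaning, from a pooled to a within-setting quantity. Timing is the one firm condition, because a change made after unblinding would look driven by the data.

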## Methods and analysis

### Study setting

Study flow, study settings and other information are presented in figure 1 and table 1. The study recruitment target is 400 participants who start ADT as primary management of de novo metastatic PCa or as secondary management for PCa recurrence after localise treatment. Participants can be high-risk M0 or M1 stage, main inclusion criterion is that long-term ADT treatment is started. These men will be randomised 1:1 (200+200) to receive either 80 mg of atorvastatin daily or placebo until disease recurrence that is, development of castration resistance, death or maximum of ten years. Sample size is based on a power calculation from a previous retrospective study.^23^

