### Study endpoints

Primary endpoint is the time to disease progression after starting ADT/antiandrogen therapy. Secondary endpoints are (1) PCa-specific mortality and overall survival, (2) change in serum cholesterol during the intervention and its role in predicting time to disease recurrence in the placebo arm, (3) occurrence of adverse tumour traits predicting development of castration resistance in circulating cell free DNA, (4) changes in fasting blood glucose during ADT, (5) occurrence of cardiovascular events during ADT and (6) Quality of life (QoL) during ADT.

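### The arm comparison of lipid change leaves out the enrolment lipid value, so it is valid but less precise than a baseline-adjusted comparison

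*Protocol article*

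**What the plan says.** Study endpoints lists as secondary endpoint 2 the "change in serum cholesterol during the intervention and its role in predicting time to disease recurrence in the placebo arm". Statistical methods fixes how the arms are to be compared: "Univariate analysis of changes in serum lipid levels is performed by calculating the difference after—before for each participant", and then "The statistical significance of the difference between the study arms is analysed by Mann-Whitney U test (or by t-test if under normality"). Boxplots accompany the test.

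The only other lipid comparison between arms is a logistic regression with study arm as the response, "whereas lipid level differences are used as predictors (ie, each lipid level difference as an independent predictor"). It too contains only differences, so the enrolment level enters neither analysis as a covariate.

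The covariate will be available. Table 2 (Study flow) has the row "Lipid levels (total cholesterol, LDL, HDL and triglycerides) (mmol/L") marked at enrolment and at 6, 12, 18 and 24 months.

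**The concern.** A man's change from baseline is negatively correlated with his baseline value unless follow-up tracks baseline perfectly, because high starting values tend to fall and low ones to rise. Subtracting the baseline therefore over-corrects for it. The over-correction adds noise to the arm contrast, which a model with the baseline as a covariate removes.

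What is at stake is precision on a named secondary endpoint. Seen within one trial, the same loss is a shift in the contrast whenever the arms happen to differ at enrolment: the arm that starts higher appears to fall more. The loss matters most for lipids where only a modest effect is in question, such as HDL and triglycerides. The stated tests also give only a p-value and a picture, where an adjusted model would give an estimate with an interval.

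**Working it through.** **Inputs from the article.** The outcome is after minus before, tested by Mann-Whitney or t-test (Statistical methods). Allocation: "These men will be randomised 1:1 (200+200"). With the assumed 10% drop-out (Sample size calculation), 200 × 0.9 = 180 men per arm remain. Alpha is 0.05, taken here as two-sided. The article gives no lipid SD, lipid effect, lipid power or baseline/follow-up correlation, so it has no figure of its own to reproduce.

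**Assumptions.** Baseline and follow-up have equal SD (set to 1) and correlation rho, shown from 0.3 to 0.9. The effect is one that a t-test on change would detect with 80% power. The article's own 80% power refers to the primary endpoint, so this is only a reference point.

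**Formulas.**
- Variance of a change score, per man: 2(1 − rho).
- Residual variance after baseline adjustment (ANCOVA): 1 − rho².
- Ratio: (1 − rho²) / [2(1 − rho)] = (1 + rho)/2. It does not depend on n.
- Power after adjustment: Φ(2.80/√((1 + rho)/2) − 1.96). At rho = 0.5: 2.80/0.866 − 1.96 = 1.27, giving about 90%.
- Expected shift of the change-score contrast for a chance baseline difference D: −(1 − rho)D.

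| rho | Variance, change | Variance, adjusted | Ratio | Power, adjusted (change: 80%) | Shift for D = 0.1 SD |
|---|---|---|---|---|---|
| 0.3 | 1.40 | 0.91 | 0.65 | 93.5% | −0.07 SD |
| 0.5 | 1.00 | 0.75 | 0.75 | 89.9% | −0.05 SD |
| 0.7 | 0.60 | 0.51 | 0.85 | 86.0% | −0.03 SD |
| 0.8 | 0.40 | 0.36 | 0.90 | 84.0% | −0.02 SD |
| 0.9 | 0.20 | 0.19 | 0.95 | 82.0% | −0.01 SD |

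**The shift and the lost precision are one thing.** The excess variance is 2(1 − rho) − (1 − rho²) = (1 − rho)², which is exactly the variance of the (1 − rho) × imbalance term. At rho = 0.5: 1.00 − 0.75 = 0.25 = 0.5². With 180 per arm, the chance baseline difference has an SD of √(2/180) = 0.105 baseline SDs. A difference of that size shifts the contrast by about 0.07, 0.05 and 0.03 SD at rho 0.3, 0.5 and 0.7.

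**Simulation, normal data, 180 per arm, rho 0.3, 0.5 and 0.7.** Power was 77%, 78% and 78% for Mann-Whitney on change, 80% each time for the t-test on change, and 93%, 90% and 86% for ANCOVA. Type I error of Mann-Whitney on change was 4.8% to 4.9%.

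**Simulation, skewed data** (log-normal, assumed log-SD 0.5; effect set to 80% power for a t-test on log change), rho 0.3, 0.5, 0.7 and 0.8. Mann-Whitney on raw change had 72%, 72%, 72% and 73% power; ANCOVA on the log scale had 93%, 89%, 85% and 84%. Part of this gain comes from the log scale rather than from the covariate.

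**The case against.** The strongest reply is that nothing here is wrong, only less efficient. Randomisation makes the change-score contrast unbiased on average, and its overall type I error is held. That stands. A reader might infer that the lipid test is biased or invalid; the documents do not support that.

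The size of the gain depends on the reference point. If the change-score test already had 95% power, the gain would be 4.4, 3.6 and 2.4 points at rho 0.3, 0.5 and 0.7; at 99% it is at most 1 point. The Introduction describes statins as cholesterol-lowering, so LDL and total cholesterol may show clearly under either method. This also stands.

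Least-squares ANCOVA is not better for every distribution. With heavy-tailed measurement noise (t with 3 degrees of freedom), Mann-Whitney on change had about 94% power at rho 0.3, 0.5, 0.7 and 0.8, against 93%, 90%, 87% and 85% for linear ANCOVA. The remedy must allow for this.

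Three further stronger readings fail:
- That the contrast carries the whole baseline imbalance: only the fraction 1 − rho is passed on, and this is not a harm additional to the lost precision.
- That the randomisation is to blame, since "No blocking or other restrictions will be implemented for randomisation": blocking would balance arm sizes, not lipid levels.
- That fasting glucose is analysed in the same way: Study endpoints names its change as endpoint 4, but Statistical methods states no test for it.

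Finally, the article promises a detailed analysis plan before final analysis, and covariates are often left to such a plan. But the article has already named the test, so the point concerns a stated choice.

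**Conclusion.** The point holds as one of efficiency. The article fixes a test on raw differences that ignores a covariate the trial already collects. Under equal SDs and normality, that test has between 1/0.65 = 1.54 times (rho 0.3) and 1/0.90 = 1.11 times (rho 0.8) the variance of a baseline-adjusted comparison. From a reference of 80% power, adjustment gains about 13.5, 10, 6 and 4 percentage points at rho 0.3, 0.5, 0.7 and 0.8, and about 2 at rho 0.9. Both rho and the 80% reference are assumptions. The endpoint is secondary; the primary log-rank analysis and the target of 400 men are unaffected. The change is worth making because it costs little and can be settled before unblinding.

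**What to change.** For each lipid, replace the two-sample test on differences with a linear model of the follow-up value at a pre-named visit on study arm and the baseline value of the same lipid. A repeated-measures model over the 6-monthly visits with the same two terms is an alternative. Use the log scale if the values are skewed. Report the adjusted arm difference with its 95% CI. If the residuals are heavy-tailed, use a rank-based or robust baseline-adjusted version, and set out that choice in advance. Keep the boxplots of change as description.

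The cost is slightly more modelling work, naming the visit, and a distributional check. No new data are needed. No men are lost beyond those a change score already excludes, since a difference also needs both values.

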Control visits are scheduled at 6-month intervals to suit common clinical practice. Control visits are done by a clinician, complemented with measurements done by a research nurse. For each control visit the participant returns remaining capsules from the previously delivered ration and will receive a new one according to his study number. Number of the remaining capsules will be counted and saved in the REDCap, trial database, to monitor compliance. In every visit, serum PSA (ng/mL), lipid levels (total cholesterol, high-density lipoprotein (HDL), low-density lipoprotein (LDL) and triglycerides, mmol/L), alkaline phosphatase (U/L), creatinine (μmol/L), and fasting glucose (mmol/L) will be measured (table 2) and the participant is asked about symptoms that are suggestive of metastases and about possible adverse effects of the study drug. Serum creatine kinase (U/L) and alanine aminotransferase (U/L) is also measured at each visit.

Blood samples are taken and stored at 6-month intervals to monitor changes in tumour markers and occurrence of adverse tumour characteristics after initiation of ADT. QoL during the intervention will be charted once a year using validated WHOQOL-BREF QoL questionnaire.^33^

Follow-up is continued until development of castration resistance, drop out from the study, death or maximum of 10 years. Participants developing castration resistance are given an opportunity to carry on with their assigned treatment as statins have been linked to longer cancer-specific survival. Unblinding will be performed after recruitment target has been reached and all participants have been followed for minimum of 12 months.

PCa treatment apart from the study drug will be up to the discretion of the attending clinician. All laboratory results, symptoms and possible imaging results will be recorded in the REDCap database. All clinical decisions regarding early chemotherapy and imaging will be made on the discretion of the clinician and recorded in the REDCap database.

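### The multivariable lipid analysis makes randomised arm the response and lipid changes the predictors, so its coefficients do not estimate atorvastatin's effect on any lipid

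*Protocol article*

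**What the plan says.** Secondary endpoint 2 in Study endpoints includes "change in serum cholesterol during the intervention". Four lipids (total cholesterol, HDL, LDL and triglycerides) are measured at enrolment and at each 6-monthly visit (Study flow and Table 2).

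Statistical methods gives two between-arm lipid analyses:

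- **Univariate.** The after-minus-before difference of each lipid is compared between arms by Mann-Whitney U test, or by t-test under normality, with boxplots.
- **Multivariable.** This is introduced as "Multivariable analysis for difference in serum lipid levels between the study arms" and carried out by "fitting a logistic regression model such that the study arm is used as the response variable whereas lipid level differences are used as predictors", with "each lipid level difference as an independent predictor". The text adds that "Lipid levels are expected to display heavy multicollinearity" and names one remedy, "possible adjustments made by dropping predictors with extreme VIFs (>10").

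The article gives the multivariable model no other purpose, such as discrimination, a global test or mediation.

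**The concern.** Arm is assigned by randomisation, and lipid change is what follows from it. A model for the between-arm difference in a lipid should therefore have the lipid on the left and arm on the right. The planned model asks whether arm can be guessed from the lipid changes, and each coefficient conditions on the other post-randomisation lipids.

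Two wrong statements could result. A lipid the drug does not change may be reported as different because it is correlated with one that does change. A lipid the drug does change may be reported as not different because a correlated lipid carries its signal. The multivariable result could then contradict the univariate one, and the article does not say which would prevail. Lipids are the first key secondary outcome listed in Table 1, and lipid metabolism as a biomarker is in the scientific title.

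**Working it through.** **Inputs.** From the article: 1:1 allocation, 200 + 200; 10% drop-out assumed per arm; available-case analysis; all lipid changes entered together; VIF cut-off 10. The article gives no lipid effect, SD or correlation and no figure for this analysis, so there is nothing to reproduce. Shifts and correlations below are assumptions, shown as ranges.

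**What the coefficients estimate.** Let the lipid changes be multivariate normal with common within-arm covariance Σ, and let δ be the vector of mean differences (atorvastatin minus placebo). Then the slopes of logit P(atorvastatin | changes) are Σ⁻¹δ, not δ. For two lipids in SD units with within-arm correlation r:

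β₁ = (δ₁ − rδ₂)/(1 − r²), β₂ = (δ₂ − rδ₁)/(1 − r²)

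- *Unaffected lipid.* δ = (−1, 0), r = 0.5: β₁ = −1/0.75 = −1.33 and β₂ = 0.5/0.75 = +0.67, although the second lipid's true difference is 0. Simulated means were −1.37 and +0.67.
- *Masked effect.* δ = (−1, −0.3), r = 0.3: β₂ = (−0.3 + 0.3)/0.91 = 0. In simulation the logistic model detected this real effect in 4% of trials; the t-test detected it in 86%.
- *Changed sign.* δ = (−1, −0.3), r = 0.5: β₂ = (−0.3 + 0.5)/0.75 = +0.27 for a lipid that truly falls.

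**How often an unaffected lipid is declared different.** Wald test at two-sided 0.05 (sidedness assumed), 200 per arm, 400 replicates per cell, so the Monte Carlo standard error is at most √(0.25/400) = 2.5 percentage points:

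| Shift in the other lipid | r = 0 | 0.1 | 0.2 | 0.3 | 0.5 |
|---|---|---|---|---|---|
| 0.5 SD | 4% | 9% | 16% | 34% | 80% |
| 1.0 SD | 6% | 14% | 44% | 80% | 100% |
| 1.5 SD | 5% | 23% | 66% | 94% | 100% |

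A further run went up to 2.9 SD (an assumed LDL fall of 2.0 mmol/L with SD 0.7: 2.0/0.7 = 2.9). Over 0.5 to 2.9 SD it gave about 3-5% at r = 0, 9-27% at r = 0.1, 15-75% at r = 0.2 and 36-98% at r = 0.3. The 34% and 36% for the same cell differ by simulation error only.

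With 180 per arm (200 × 0.9) the rates barely move: 77% at 1.0 SD and r = 0.3. With 100 per arm they fall to about 6-15%, 11-47% and 20-83% at r = 0.1, 0.2 and 0.3. On the two-lipid simulated data, the t-test and Mann-Whitney test of the unaffected lipid rejected in 2.5% to 7.2% of trials, which is nominal within simulation error.

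**Does the VIF rule help?** For two predictors VIF = 1/(1 − r²). At r = 0.5 this is 1/0.75 = 1.33, and reaching 10 needs r = √0.9 = 0.95. The rule therefore does not act in any cell above. In a four-lipid example (assumed effects: LDL −1.5, HDL 0, triglycerides −0.3 mmol/L; total cholesterol as their near-sum) the rule always removed total cholesterol. HDL was still falsely declared different in 7%, 74% and 98% of trials at LDL-HDL correlations of 0, 0.2 and 0.3.

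**Baseline adjustment, a separate matter.** The variance ratio of ANCOVA to change score is (1 − ρ²)/(2(1 − ρ)) = (1 + ρ)/2, where ρ is the baseline-to-follow-up correlation. For assumed ρ = 0.7 it is 0.85 and for ρ = 0.3 it is 0.65, that is, 15% to 35% less variance.

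**The case against.** The strongest reply is that a valid analysis is already planned. The univariate step compares each lipid's change between randomised arms, holds its 5% level, and addresses the change-in-cholesterol part of endpoint 2. This stands. A reader might infer that the plan cannot answer that part of the endpoint, or that a lipid dropped for its VIF goes unreported. Neither follows, because the univariate test still reports every lipid.

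Second, the inflation is conditional. A reader might infer that the model is bound to declare false differences. The article does not support that: it gives no correlations and names no lipid as unaffected. Its expectation of heavy multicollinearity may refer mainly to total cholesterol overlapping with its fractions. At r = 0 the error is near nominal, and if the drug changes no lipid the model also keeps its level (4.9% and 4.4% in simulation). Follow-up ends at castration resistance and analyses use available data, so later visits may have fewer men and less inflation. All of this stands as a limit on size. It does not change what the coefficients estimate.

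Third, the logistic coefficient does test something true, namely association with arm given the other lipids. That is right, and the error lies in presenting it as a difference in lipid levels between arms, which is how the article labels it.

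Fourth, the damage done by the VIF rule is easily overstated. With total cholesterol simulated as LDL + HDL + TG/2.2 plus noise, VIFs are about 100-120 at a noise SD of 0.1, about 10-12 at 0.3 and about 8 at 0.4. Whether the rule acts depends on that assumption, and the article speaks only of possible adjustments. The point made here is only that the rule does not prevent the distortion.

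**Conclusion.** The model is wrong as written for its stated purpose. Its coefficients are conditional log-odds of arm and do not estimate atorvastatin's effect on a lipid. That conclusion needs no assumed effect size: the two sets of numbers answer different questions and coincide only in special cases.

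The size of the resulting error does rest on assumptions: approximately normal changes, a non-zero within-arm correlation, a clear shift in at least one lipid and no effect on another. Under these, false declarations run from modestly to far above 5%, and a real effect can be hidden.

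The consequence is confined to the multivariable result for part of secondary endpoint 2. The univariate tests are valid and the log-rank analysis of the primary endpoint is unaffected. A reader might also take the after-minus-before differences to be biased. Under randomisation they are not; adjusting for baseline gains precision only.

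**What to change.** Replace the logistic model. For each lipid, fit a model with the lipid as outcome and arm plus that lipid's baseline value as predictors: either ANCOVA at a named visit or a mixed model over the 6-monthly visits. Report the adjusted mean difference with its 95% CI for each lipid. Drop the VIF rule, since the lipids are no longer joint predictors.

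If the logistic model is kept, label it as a global or descriptive check only, and state that its coefficients will not be read as drug effects.

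The cost is wording. Baseline and 6-monthly lipids are already scheduled, and the article says that a detailed analysis plan will be published before the final analysis, so the change can be made there.
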